## Abstract

**Background:**

Osteoporosis is a debilitating disease and its risk can be reduced through adequate calcium consumption and physical activity. This protocol paper describes a workplace-based intervention targeting behaviour change in premenopausal women working in sedentary occupations.

**Method/Design:**

A cluster-randomised design was used, comparing the efficacy of a tailored intervention to standard care. Workplaces were the clusters and units of randomisation and intervention. Sample size calculations incorporated the cluster design. Final number of clusters was determined to be 16, based on a cluster size of 20 and calcium intake parameters (effect size 250 mg, ICC 0.5 and standard deviation 290 mg) as it required the highest number of clusters.

Sixteen workplaces were recruited from a pool of 97 workplaces and randomly assigned to intervention and control arms (eight in each). Women meeting specified inclusion criteria were then recruited to participate. Workplaces in the intervention arm received three participatory workshops and organisation wide educational activities. Workplaces in the control/standard care arm received print resources. Intervention workshops were guided by self-efficacy theory and included participatory activities such as goal setting, problem solving, local food sampling, exercise trials, group discussion and behaviour feedback.

Outcomes measures were calcium intake (milligrams/day) and physical activity level (duration: minutes/week), measured at baseline, four weeks and six months post intervention.

**Discussion:**

This study addresses the current lack of evidence for behaviour change interventions focussing on osteoporosis prevention. It addresses missed opportunities of using workplaces as a platform to target high-risk individuals with sedentary occupations. The intervention was designed to modify behaviour levels to bring about risk reduction. It is the first to address dietary and physical activity components each with unique intervention strategies in the context of osteoporosis prevention. The intervention used locally relevant behavioural strategies previously shown to support good outcomes in other countries. The combination of these elements have not been incorporated in similar studies in the past, supporting the study hypothesis that the intervention will be more efficacious than standard practice in osteoporosis prevention through improvements in calcium intake and physical activity.

## Background

Osteoporosis is a disease characterised by bone fragility due to low bone mass and a break down in the skeletal framework. It is a major public health problem affecting millions of people worldwide, with significant physical, psychosocial and financial consequences for the patient and the health care system
[1]. Women are at higher risk of getting osteoporosis due to attainment of lower peak bone mass early in life and hormonal changes that occur at the menopause
[1,2].

While osteoporosis is a disease with a strong genetic predisposition, calcium intake and physical activity are well-established modifiable risk factors operating through the maintenance of bone mass and skeletal integrity
[1,2]. Evidence suggests that physical activity and calcium intake can affect not just bone mineral density, but also risk of osteoporotic fractures
[3,4]. Prospective longitudinal studies have estimated that 23% of osteoporosis is attributable to physical inactivity
[3] and that almost 10% of osteoporotic fractures are attributable to low dietary calcium intake
[4]. This demonstrates that there are substantial preventable fractions on the order of 10% - 20% for osteoporosis and osteoporotic fractures, and that efforts to develop intervention strategies to achieve this are warranted, thus prompting recommendations for population-based interventions to promote adequate calcium intake and physical activity to prevent osteoporosis.

### Limitations in current evidence base

The majority of health promotion studies addressing osteoporosis prevention suffer from weak intervention designs and lack of methodological rigour. Many intervention strategies did not appear to be guided by behaviour change theory. None appear to have referenced past evidence to determine the level of behaviour change that is required to make an impact on the disease and its consequences
[5-8]. Some interventions consisted of one-off information sessions or print resource distribution
[5,9].

i) Single behaviour versus multiple behaviour approaches

None of the studies targeting osteoporosis prevention behaviours have attempted to approach the dietary and physical activity components separately. They adopted the same intervention strategies for both behaviours and did not appear to have incorporated unique strategies for either behaviour into their intervention design. These interventions reported modest or no increases in calcium intake in the short-term
[5-7,10] and generally poor physical activity outcomes
[5,10-12].

Evidence suggests that single health behaviour interventions were more effective at improving the targeted behaviours than multiple behaviour interventions
[13]. Interventions that have singularly targeted dietary calcium intake for women have consistently reported positive outcomes
[14,15]. Positive outcomes are also often reported in intervention studies specifically targeting general physical activity
[16,17]. Few physical activity behaviour interventions have been carried out in the context of bone health in adult populations. Prescriptive exercise interventions for adults, which included load bearing activity of moderate to vigorous intensity, have reported strong positive associations with improved bone mass
[18]. However, prescriptive exercise interventions only engage participants in regimented exercise and do not address participants’ attitudes or barriers towards adopting physical activity. Such interventions consistently suffer high attrition rates and are not suited for implementation at the population level.

ii) Cognitive versus behavioural strategies

A meta-analysis of physical activity interventions suggests that behavioural strategies (such as goal setting, problem solving) are superior to cognitive strategies
[19]. Taken together, these studies suggest that an osteoporosis prevention intervention design should place specific emphasis on behavioural strategies targeting calcium intake and physical activity as unique and distinct health behaviours.

iii) Occupational settings

Workplaces are valuable settings for the efficient delivery of preventive health intervention programs to healthy adult populations. Women in sedentary occupations are a priority group for osteoporosis prevention, as being both female and sedentary are independent risk factors for low bone mass and osteoporosis. Occupational sitting has been associated with low bone mineral density of the hip
[20]. Workplaces with predominantly sedentary employees present great opportunities to address behaviours that can decrease the risk of osteoporosis. There are no published studies to date on workplace-based osteoporosis prevention programs. While most studies targeted women in the community, none of them targeted those with sedentary occupations.

iv) Osteoporosis prevention studies in Singapore

Research resources on osteoporosis prevention in Singapore were predominantly allocated to bio-medical interventions at the time of this Singapore-based study. Relevant health promotion studies in Singapore were limited and predominantly investigated knowledge and attitudes. No local studies had previously investigated the efficacy of behaviour strategies for osteoporosis prevention.

### Importance of this study for osteoporosis prevention at population level

Existing evidence points to unrealised potential in both intervention design and settings when addressing osteoporosis prevention. This study improves on previous research as follows:

1. It is the first to address dietary and physical activity components each with unique intervention strategies in the context of osteoporosis prevention.

2. The intervention design for both behaviours is guided by Bandura's self-efficacy theory. The design focused on behavioural strategies rather than cognitive strategies to increase subjects' self-efficacy to change behaviour.

3. The utilisation of a workplace platform to address the risk associated with low levels of physical activity at work.

4. The use of an evidence-based approach when setting the intervention outcomes. Targeted behavioural outcomes were supported by evidence with the potential to affect the burden of osteoporosis.

5. This study compared a strengthened intervention design to a standard care control, which was current conservative practice. The results would indicate the degree to which the intervention design improves on current practice.

### Aims

The overall aim of this study was to determine the efficacy of a tailored and self-efficacy focussed workplace-based intervention compared with standard care (print resources) in increasing the calcium intake and physical activity level of women with sedentary occupations.

The specific objectives were:

1. To test the hypothesis that a tailored workplace based intervention incorporating specific behavioural strategies for calcium intake and physical activity is more efficacious than standard care (simple print resource distribution) in increasing the calcium intake and physical activity levels.

2. To explore the relationship between self-efficacy scores for calcium intake and physical activity with actual calcium intake and physical activity levels to determine the extent to which self-efficacy mediates intervention-associated changes in calcium intake and physical activity.

### Study design

This was a prospective two-arm cluster randomised trial. Clusters were workplaces that were randomly assigned to receive either i) tailored workplace-based intervention or ii) print resources (standard care control arm).

### Specification of intervention targets

i) Calcium Intake

In 2004, the Singapore National Nutrition Survey reported the mean daily calcium intake of the female population as 598 milligrams
[21]. This level of calcium consumption was below the recommended daily allowance (RDA) of 800 milligrams for 25 to 44 year old women who constituted the main target group for the study. The survey reported that 55.9% of the Singapore female population did not achieve sufficient calcium intake (defined as <70% of RDA) through their diet
[21]. Fifty percent of women in the premenopausal age group (30 to 49 years old) had daily intake of 560.5 mg or less (range 258 mg to 565 mg)
[21]. We anticipated that the women in our study were similar, and that a deficit of at least 250 mg needs to be corrected. This assumption would be tested through assessment of baseline calcium intake from both intervention groups.

Evidence supports the health significance of this study’s proposed effect size for calcium intake. Warensjo et al. (2011) reported on a 19 year follow up on 61,433 Sweden women and found that almost 10% of hip fracture may be attributable to low calcium intake (first quintile)
[4]. It is important to note that the first quintile in this study was reported to be less than 759 mg per day
[4]. This is high compared to Singapore female population where the mean intake in the first quartile is 411 mg per day
[21]. Population attributable risk is potentially higher in the Singaporean female population due to lower calcium intake (e.g. because of lower dairy intake compared to Sweden). According to Warensjo et al. (2011), population attributable risk (%) of hip fracture decreased by 3.34% with every 300 mg increase in calcium intake
[4].

This is further supported by studies in another population with calcium intake comparable to Singapore. Rouzi et al. (2012) studied independent predictors of all osteoporosis-related fractures among 707 healthy Saudi postmenopausal women over 5.5 years. They reported a mean daily calcium intake of 532 milligrams in their study population; very similar to the 598 milligrams reported in Singapore's female population
[22]. The study estimated that 26.4% of osteoporotic fractures are independently attributable to low dietary calcium intake (<391 mg/day)
[23]. The reported osteoporotic fracture relative risk (RR) is 1.66 for a low dietary calcium intake (<=391 mg/day) when compared to a higher intake (>/=648 mg/day)
[23].

In Hong Kong, Lau et al. (1988) reported hip fracture RR to be 1.9 when comparing calcium intake in the lowest quintile (<75 mg/day) to the highest quintile (>244 mg/day)
[24]. Chan et al. (1998) reported the odds of vertebra fracture to double (OR = 2.1) when dietary calcium intake was in the lowest quartile (<249 mg/day) compared to the highest quartile (>382 mg/day)
[25].

Calcium consumption in the Asian population appears to be lower than in Europe
[4,23-25], supporting a particular need for intervention in low calcium intake (e.g., many Asian) populations. Evidence has demonstrated that even a modest increase in calcium intake (in the range of 120-150 mg) can have substantial impact on osteoporotic fracture risk
[23-25].

Past interventions have demonstrated that the effect size of 250 mg is achievable. Osteoporosis prevention studies that focused only on dietary interventions and incorporated strong behavioural strategies reported significant increases in calcium intake (200-300 mg) compared to controls
[14,15].

ii) Physical activity

The Singapore National Health Survey in 2004 reported that 54.5% of the female population does not participate in leisure physical activity
[22]. Only 18.8% of women in the pre-menopausal age group (30 to 49 years old) reported at least 60 minutes of physical activity per week
[22]. The World Health Organisation (WHO) recommends that adults aged 18–64 should do at least 150 minutes of moderate-intensity aerobic physical activity throughout the week or do at least 75 minutes of vigorous-intensity aerobic physical activity throughout the week
[26]. This means that majority of Singapore's female physical activity level falls well below the recommended guidelines. We anticipated that the women in our study sample would have a similar physical activity profile.

This study's intervention content was aimed at supporting participants to achieve a 60-minute increase in load-bearing physical activity of moderate to vigorous intensity. Evidence suggests that the risk of hip fracture declines 6% for every increase of 3 MET hr/week, which is equivalent to 60 minutes per week walking at an average pace
[27].

A larger effect size was initially considered. However, participants in this study were anticipated to have very low physical activity at baseline. WHO recommendations state that inactive people should start with small amounts of physical activity and gradually increase duration, frequency and intensity over time
[26]. Moreover, this study targets a domain of physical activity that is more site-specific and higher in intensity, hence potentially more challenging to adopt.

Large worksite interventions to increase general physical activity have reported a wide variation in improvements. Reported increases in moderate to vigorous intensity physical activity per week range from 40 to 300 minutes
[28,29]. Differences in intervention design and duration might account for this variability. Notably, none of these workplace based studies were designed for osteoporosis prevention. None of the studies investigating osteoporosis prevention behaviours reported physical activity outcomes in duration or intensity.

In summary, the effect size of 60 minutes of moderate to vigorous intensity load -bearing physical activity is achievable for a workplace-based intervention, and has the potential to meaningfully reduce the risk of osteoporosis.

### Sample size calculation

Sample size calculations took into consideration the cluster randomisation design by incorporating the design effect into the calculation. The design effect was calculated based on a cluster size of 20 and the intracluster correlation coefficient (ICC) using the formula: Design Effect = 1 + (within cluster sample size −1) x ICC. In the absence of ICCs for the outcome measures, available population standard deviations were used to calculate the variances and the ICC using the formula: ICC = variance between cluster/(variance between cluster + variance within cluster). In this study, there were two primary outcome measures, calcium intake and physical activity. Sample size calculations were carried out for both measures. Calculations were based on α = 0.05 and β = 0.1. Table 
1 shows the parameters used for calculating the number of clusters and the total number of participants. The study deliberately planned to over recruit within clusters to factor in a 30% attrition rate.

**Table 1 T1:** Summary of parameters used in the sample size calculation

**Outcome measures and mediators**	**Effect size**	**ICC used in sample size calculation**	**Standard deviation used in sample size calculation**	**Design effect**	**Number of clusters**	**Total subjects to be recruited**	
						**Before factoring in 30%****attrition**	**After factoring in 30%****attrition**
Calcium intake (milligrams per day)	250 milligrams	0.5*	290 milligrams***	10.5	14.7	294	480
Physical activity duration (minutes per week)	60 minutes	0.05**	150 minutes****	1.95	13	255	420

*Calculated using standard deviation from National Nutrition Survey 1998 and based on conservative estimates of inter- and intra-cluster variance
[23].

**Based on estimates from published studies
[30,31].

***Estimate from National Nutrition Survey 1998
[32].

****Based on estimates from published studies
[33,34].

The number of clusters required was different for each outcome measure, so the study was based on the highest number of clusters required, which was that for calcium intake (14.7). This was rounded up to 16 to ensure equal cluster numbers in both arms of this study.

There was an error in the final step of this study's sample size calculations. The calculation did not double the sample size calculation that yielded the number of required subjects per arm (for this two-arm study). The sample size calculation, however, was very conservative with the ICC estimates and the study was expected to be overpowered despite the omission of this step. This study still has 90% power to detect 355 milligrams increase in calcium intake and 85 minutes increase in moderate to vigorous intensity physical activity with 16 clusters of 20 participants per cluster.

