### Limitations

The outcomes measures in this study were all derived from self-reports, which may incur potential bias. Steps were taken in this study to ensure the self-report measurement tools in this study were valid and reliable for the study population. Nevertheless, the osteoporosis preventive potential of the intervention would be more accurately and precisely assessed using objective bone mass density or other biomarker measures. However, resource and feasibility limitations excluded these possibilities. This is an important consideration for future studies in this area.

This study utilised the social structure and existing infrastructure within workplaces to deliver the interventions, but it did not have the capacity to influence workplace policies and practices to address sedentarism at the organisational level. This is a limitation in the study and an important consideration for future research, as intervention strategies to reduce workplace sitting time are rapidly developing.

At the time of the study, published ICC values for the targeted outcome and mediators were either limited or absent. In the absence of published ICCs, we adopted a conservative approach of assuming large ICCs in the calculations. This might have inflated the required number of clusters. However, it is also possible that the study will be underpowered to account for potential confounding. We will publish the observed ICC values for calcium intake, physical activity measures and self-efficacy scores in the reporting of the main results of the study. A retrospective calculation of the number of clusters and power based on the actual observed ICCs will be reported to compare with the original estimates.

High attrition rate is often a problem in population based intervention studies. A higher dropout rate is anticipated in this study because of loss of subjects through work factors such resignation and corporate restructuring. In an attempt to maintain cluster sizes, there was deliberate over-recruitment of within cluster subjects by 30 percent. However, some degree of selection bias may occur if attrition is high.

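### The article expects the trial to be overpowered, but at its own tabulated ICCs 16 workplaces give about 60–66% power for 250 mg calcium and 66–73% for 60 minutes of activity, and Table 1 still labels per-arm numbers as totals

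*Protocol article*

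**What the plan says.** Under Sample size calculation, the article names two primary outcomes and sets the error rates: "Calculations were based on α = 0.05 and β = 0.1". Table 1 gives an effect of 250 mg, ICC 0.5, SD 290 mg and design effect 10.5 for calcium. For physical activity it gives 60 minutes, ICC 0.05, SD 150 minutes and design effect 1.95. The resulting 14.7 and 13 clusters, and 294 and 255 women before attrition, stand in columns for the number of clusters and the total to be recruited. Of the 14.7 the text says: "This was rounded up to 16 to ensure equal cluster numbers in both arms of this study". The Abstract repeats the derivation: "Final number of clusters was determined to be 16, based on a cluster size of 20 and calcium intake parameters".

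The section then discloses that the last step, doubling the per-arm figure, was left out. It adds that "the study was expected to be overpowered despite the omission of this step", citing very conservative ICCs, and next gives 90% power for 355 mg and 85 minutes with 16 clusters of 20. Limitations returns to the ICCs: "we adopted a conservative approach of assuming large ICCs in the calculations". The footnotes to Table 1 differ on this. The calcium ICC is said to rest on conservative variance estimates, and the activity ICC on published studies.

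**The concern.** A design that reaches 90% power only at effects about 1.4 times its targets is not overpowered for those targets at the inputs it was planned on. The article gives the two enlarged effects but never the power at 250 mg and 60 minutes, so the reader meets a reassurance where the less favourable figure belongs. Both outcomes are primary. Someone who accepts the reassurance could take a non-significant result as good evidence against an effect of the planned size.

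For calcium, 355 mg also lies above the range the article uses to argue feasibility: earlier dietary studies "reported significant increases in calcium intake (200-300 mg) compared to controls". Table 1 adds to the problem because its labels were not changed when the error was disclosed. A reader who looks only at the table sees 294 women and 14.7 clusters as the full requirement.

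**Working it through.** **Inputs.** The Abstract gives "calcium intake parameters (effect size 250 mg, ICC 0.5 and standard deviation 290 mg"; Table 1 agrees and adds activity SD 150 minutes and ICC 0.05. The activity target is in Specification of intervention targets: "the effect size of 60 minutes of moderate to vigorous intensity load -bearing physical activity is achievable". Cluster size is m = 20, with 8 workplaces and so 160 women analysed per arm. Alpha is 0.05, taken as two-sided because one-sided gives 242 and 209 per arm and does not reproduce the table. The planned analysis is a cluster-level t-test, with 16 − 2 = 14 df.

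**Reproducing Table 1.** n per arm = 2 × (1.960 + 1.2816)² × SD² / δ² × DE, where DE = 1 + (m − 1) × ICC.

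- Calcium: 28.28 × 10.5 = 296.9. Using 28 gives exactly 294, and 294 / 20 = 14.7.
- Activity: 131.3 × 1.95 = 256.1, and 256.1 / 20 = 12.8. The table has 255 and 13.

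Both match, and both are numbers per arm.

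**Power with 8 × 20 per arm.** SE of the difference = SD × √(2 × DE / 160).

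- Calcium: 290 × √(2 × 10.5 / 160) = 105.1 mg.
- Activity: 150 × √(2 × 1.95 / 160) = 23.4 minutes.

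Normal power is Φ(δ/SE − 1.96). The t column uses the noncentral t with 14 df.

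| Effect | Normal | t, 14 df |
|---|---|---|
| 250 mg (planned) | 66% | 60% |
| 60 min (planned) | 73% | 66% |
| 355 mg (restated) | 92% | 88% |
| 85 min (restated) | 95% | 92% |

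The restated effects are close to √2 times the targets (353.6 mg and 84.9 min) and are roughly right. The effects detectable with 90% power are 341–367 mg and 76–82 minutes. Even if all 30 women recruited per workplace were analysed, power at the targets would be only 61–67% and 74–80%.

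**ICC needed for 90% at the planned effects.** ICC = [(δ/k)² × 160 / (2 × SD²) − 1] / 19, with k = 3.2415 (normal) or 3.489 (t, 14 df).

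- Calcium: 0.245 (normal) or 0.204 (t), against 0.5 assumed.
- Activity: 0.011 (normal) or 0.003 (t), against 0.05 assumed. At ICC = 0, power is 95% (normal) or 91% (t).

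**Totals for 90%.** Doubling Table 1 gives 2 × 294 = 588 and 2 × 255 = 510 women. By the normal approximation that is 2 × 14.7 = 29.4, so 30 workplaces, and 2 × 13 = 26. The cluster-level t-test needs 16 and 14 per arm, so 32 and 28.

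**The case against.** The error is disclosed, and 90% power is moved at once to 355 mg and 85 minutes. That stands. A reader might infer that the article still claims 90% at 250 mg and 60 minutes, or that the Abstract does. The documents do not support this: 90% at the targets is the original plan, and the Abstract states no power.

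The reassurance can also be read as an expectation under ICCs smaller than those tabulated, so it need not flatly contradict the sentence after it. For calcium this has force. Table 1 calls the basis of 0.5 conservative, and at a true ICC of 0.20 power at 250 mg would be 94% (normal) or 90% (t). The true value is not known from the article, so 60–66% should not be read as the power the trial certainly has.

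For activity the argument is weak. It would be too strong to say that it cannot apply, since a high value might have been picked from the published studies. But the ICC would have to fall from 0.05 to about 0.01 or less, and nothing in the article suggests that.

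The planned analysis adjusts for baseline, which could recover power. As an assumption, adjustment that removed 46–53% of the variance of the calcium difference, or 38–46% for activity, would restore 90% at the tabulated ICCs. The article gives no correlation and does not use this argument.

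Limitations concedes possible underpowering to account for confounding, and promises observed ICCs and a retrospective power calculation. Those are useful commitments, but they neither withdraw the reassurance nor address the missing doubling.

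**Conclusion.** The point holds as a correction of wording and labelling to a disclosed error. At the tabulated ICCs and SDs, with 20 women analysed in each of 8 workplaces per arm and no credit for baseline adjustment, power is 60–66% for the calcium target and 66–73% for the activity target, against 90% planned. The expectation of being overpowered is unsupported for activity, where even an ICC of zero gives only 91–95%. For calcium it is conditional on a true ICC of about 0.20–0.25 or lower. Table 1's subject and cluster columns are per-arm figures under headings that present them as totals.

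A reader might go further and say that each primary outcome carries at least a one-in-three chance of missing its target effect. That holds for calcium at the tabulated ICC (34–40%) but not throughout for activity (27–34%).

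**What to change.** - In Sample size calculation, delete the expectation of being overpowered, or limit it to calcium and state the ICC on which it depends.
- In the same section, state the power of 16 workplaces of 20 at the planned effects and ICCs: about 60–66% for 250 mg and 66–73% for 60 minutes. Give the ICC at which 90% would be reached: about 0.20–0.25 and 0.003–0.011. Say that baseline adjustment is not counted.
- In Table 1, label 294/255 and 14.7/13 as per arm and add the totals: about 588 and 510 women before attrition, in 30 and 26 workplaces by the normal approximation, or 32 and 28 workplaces for the planned t-test.
- Correct the after-attrition column to match. The present 480 and 420 equal 16 × 30 and 14 × 30. On the same basis of 30 recruited per workplace, the totals become 900 and 780 (normal) or 960 and 840 (t-test).

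These totals show what the 90% plan would have required; they do not call for more recruitment. No participant, procedure or analysis changes, and the only cost is a less favourable stated power. A rule for reading non-significant results from the confidence interval would be an optional addition and is not part of this correction.

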#### Within cluster recruitment (individuals)

When the workplace (cluster) allocation process was completed, workplace coordinators from both groups were contacted to commence the within-cluster recruitment process. The coordinator was provided with resources (such as posters, e-mailers) to publicise the recruitment. Employees who expressed interest were screened for eligibility before being recruited into the study. Over-recruitment by 30 percent to account for attrition was planned. Workplaces that recruited more than 30 respondents would create a waiting list in the event of withdrawal before commencement. Workplaces with less than 30 respondents would include all eligible respondents in the study.

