### Cluster level analysis that adjusts for individual covariates and baseline measures

The main hypotheses will be tested using cluster-level analyses. This approach adheres to the recommendation of the 2004 Consort Statement for cluster randomised trials to fully account for the clustering effect
[46,47] and is recommended for studies with small number of clusters
[47,48]. Individual-level analysis using multi-level/mixed models was considered, but this study does not have the required cluster numbers for multilevel modelling as recommended by some analysts (minimum recommended is 15 cluster per arm)
[47].

This study will use the two-stage adjusted analysis based on cluster summaries developed by Hayes and Moulten (2009, pp182-184)
[47]. In stage one, SPSS linear regression will be run to generate an unstandardised residual for each subject (the difference between the observed value and the fitted value from the model for each individual participant). Baseline calcium value for each subject will be controlled for in the linear regression model. Other variables that were identified as potential confounders will also be included in the model as factors or covariates. This step incorporates repeated measures into the analysis and generates the covariate-adjusted residuals for each individual.

Cluster summaries for the covariate-adjusted residuals are then generated using SPSS descriptive statistics. These summaries are for stage two of the analysis, which is the cluster level analysis. The cluster means of the residuals are then compared in a cluster level analysis using a weighted *t*-test, with weighting based on cluster size (number of participants per cluster).

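### The restated detectable effects of 355 mg and 85 min belong to totals of 294 and 255 women, not to the 16 workplaces of 20 (320 women) named in the sentence

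*Protocol article*

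**What the plan says.** All of this is in the protocol article. Under Sample size calculation: "Calculations were based on α = 0.05 and β = 0.1". Table 1 gives totals before attrition of 294 women (14.7 clusters) for calcium and 255 (13 clusters) for physical activity, and 480 and 420 after attrition. The larger cluster number is rounded up to 16.

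The section then concedes that these totals were in fact per-arm numbers that had not been doubled. It restates what the trial can detect: "This study still has 90% power to detect 355 milligrams increase in calcium intake and 85 minutes increase" in activity, "with 16 clusters of 20 participants per cluster".

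On attrition, the same section says "The study deliberately planned to over recruit within clusters to factor in a 30% attrition rate", and Within cluster recruitment says "Over-recruitment by 30 percent to account for attrition was planned". Limitations repeats the 30 percent. The workplace inclusion criteria and the waiting-list rule both work with 30 women per workplace.

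The main test is a weighted t-test on cluster means of covariate-adjusted residuals, "with weighting based on cluster size (number of participants per cluster".

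**The concern.** The sentence was written to repair an acknowledged error, and it is the only corrected power statement in the article. It names one design, 16 x 20 = 320 women, so both detectable effects should follow from 320. They do not. Each matches the uncorrected total in its own row of Table 1.

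The consequence lies mainly in reporting. Limitations promises a retrospective calculation of clusters and power, to be set against the planning estimates. If those estimates are tied to the wrong sample, the comparison in the main results paper starts from the wrong baseline. A reader also cannot tell from the sentence whether the figures refer to a normal approximation or to the cluster-level t-test that will be used.

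**Working it through.** **Inputs.** Calcium: "calcium intake parameters (effect size 250 mg, ICC 0.5 and standard deviation 290 mg"), from the abstract and Table 1. Activity: "the effect size of 60 minutes of moderate to vigorous intensity load -bearing physical activity" from Specification of intervention targets, with ICC 0.05 and SD 150 min from Table 1. Cluster size is 20, alpha 0.05 and power 90%. Sidedness is not stated. Two-sided is assumed because, among the standard variants tried, only it gives Table 1's numbers.

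**Design effects.** 1 + 19 x 0.5 = 10.5 and 1 + 19 x 0.05 = 1.95, as in Table 1.

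**Table 1 reproduced.** n per arm = 2 x (1.960 + 1.282)² x (SD/effect)² x DE, where (1.960 + 1.282)² is about 10.507.
- Calcium: 2 x 10.507 x (290/250)² x 10.5 = 296.9 per arm. Without the design effect it is 28.28, and 28 x 10.5 = 294.
- Activity: 2 x 10.507 x (150/60)² x 1.95 = 256.1 per arm. Without the design effect it is 131.34, and 131 x 1.95 = 255.45.

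So 294 and 255 are per-arm numbers, which confirms the missing doubling that the article admits.

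**Detectable effects.** Effect = multiplier x SD x sqrt(2 x DE / n per arm). The multiplier is 1.960 + 1.282 for the normal approximation. For 14 df it is close to 2.145 + 1.345 = 3.490; an exact noncentral-t calculation agrees.

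| Total women | Method | Calcium | Activity |
|---|---|---|---|
| 294 | normal | 355.3 mg | 79.2 min |
| 255 | normal | 381.5 mg | 85.0 min |
| 320 (16 x 20) | normal | 340.6 mg | 75.9 min |
| 320 (16 x 20) | t, 14 df | 366.6 mg | 81.7 min |

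The t row uses the unadjusted SDs and equal cluster sizes. The stated pair, 355 and 85, takes calcium from the first row and activity from the second.

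**Does another method rescue the pair?** At one common sample the multiplier and n cancel, so the ratio of the two detectable effects is fixed: 290 x sqrt(10.5) / (150 x sqrt(1.95)) = 4.49. The stated ratio is 355/85 = 4.18. If both figures had been rounded to the nearest 5, the ratio could reach only 357.5/82.5 = 4.33. With Table 1's inputs, no single choice of alpha, power or reference distribution at 16 x 20 gives both figures.

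**Power of 16 x 20 at the stated effects.**
- 355 mg: 92.2% (normal), 88.1% (t, 14 df).
- 85 min: 95.3% (normal), 92.1% (t, 14 df).

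**Attrition column.** 294/0.7 = 420 and 255/0.7 = 364, against 480 and 420 in Table 1. Multiplying by 1.3 instead gives 382 and 332. The stated totals equal 16 x 30 and 14 x 30, that is, an even number of workplaces times 30 recruits. This derivation is inferred; the article does not give it. Going from 30 to 20 is an allowance of 33%, and 30 x 0.7 = 21.

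**The case against.** The best defence is that the sentence remains true if read as at least 90% power. Under the protocol's own design-effect method, 16 x 20 has 92% power for 355 mg and 95% for 85 min, so both figures err on the safe side. This stands, and it limits the size of the point. It does not make them the figures for 16 x 20.

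A reader might go further and infer that the calcium claim is too optimistic for the planned test, because the 14-df t-test needs 367 mg. The documents do not support that. The 367 mg pairs the t distribution with an unadjusted survey SD, whereas the planned analysis first removes variation explained by baseline and other covariates. Since (355/366.6)² = 0.938, a reduction of just over 6% in the variance of the cluster means would bring the requirement down to 355 mg. The article gives no baseline correlation, so the true value is unknown. For the same reason, 367 mg and 82 min must not be presented as the detectable effects of the planned analysis.

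A reader might also infer that over-recruiting by 30 percent means 26 women per workplace (20 x 1.3), leaving 18.2 after 30% loss. That does not hold either: 26 appears nowhere, and the article works with 30 per workplace, which leaves 21. The attrition point is therefore one of labelling and not a shortfall in the plan.

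Finally, the article openly admits the missing doubling, calls its ICCs deliberately large, and promises power recalculated from the observed ICCs. This is fair, but it does not correct the sentence.

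**Conclusion.** The point holds as an arithmetic misattribution. The 355 mg and 85 min are normal-approximation results for 294 and 255 women, attached to a design of 320. The figures for 16 x 20 are about 341 mg and 76 min by the protocol's method, or about 367 mg and 82 min on an unadjusted 14-df t-test. The stated calcium figure is thus about 4% above the first and 3% below the second; the activity figure is about 12% and 4% above.

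This rests on two-sided alpha 0.05, Table 1's SDs and ICCs, and 20 analysed women in every workplace. It does not show that the trial is less able to detect 355 mg than claimed under its adjusted analysis. No decision on design, eligibility or analysis turns on it. The attrition totals are mislabelled, but the target of 30 per workplace is adequate for 20 after 30% loss.

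**What to change.** In Sample size calculation, restate the corrected power sentence for 16 workplaces of 20 analysed women, with method and assumptions named:
- about 341 mg and 76 min at 90% power by the normal approximation with two-sided alpha 0.05;
- about 367 mg and 82 min for a 14-df t-test on cluster means, without baseline adjustment and with equal cluster sizes;
- a note that baseline adjustment is expected to lower these values by an amount not known at planning.

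In Table 1, label the last column as workplaces (rounded to an even number) times 30 recruits. In Sample size calculation, Within cluster recruitment and Limitations, replace the 30 percent over-recruitment wording with the rule used: a target of 30 recruits per workplace, to retain at least 20 after 30% loss.

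The cost is a correction to text and one table heading. Recruitment, randomisation and analysis are unaffected.
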